##### Certainty (“risk”) assessment and delivery of the intervention

The study coordinator will collect pre-intervention variables from patients, including the components of the STONE score [8]. The coordinator will collect and collate relevant variables from the clinician, including ultrasound results. The clinician will receive a document clarifying the patient’s STONE score and the meaning of that score (Ex. Moderate STONE score + mild hydronephrosis = 90% chance of stone) (see Supplementary Material 2). The study coordinator will then provide the clinician with a color copy of the decision aid to provide a concise refresher of the content. There are two areas of the decision aid where the clinician will be prompted to enter data personalized to the patient. First, they will be prompted to fill in a line about pre-test probability, based on the STONE Score and the ultrasound results. Second, they will be given the option of indicating their recommendation prior to the conversation. The decision aid will then be given to the patient, and the study coordinator will give the patient at least 15 min to read the decision aid prior to discussion with the clinician. The treating clinician will then, using the KSC decision aid as a tool to facilitate a conversation, educate the patient regarding the rationale for their clinical suspicion up to that point in the ED visit and engage the patient in a shared decision regarding whether to obtain a CT at that time.

##### Usual care

Participants in the usual care group will receive an informational intervention. This two-page pamphlet contains relevant information about kidney stones developed as part of the decision aid development process, but does not address decision-making or the use of CT scans. Clinicians who have a patient in the usual care group will be encouraged to continue care as usual. Stakeholder engagement has suggested usual care may include the use of CT, ultrasound, and/or shared decision-making. The usual care group will not have access to the decision aid.

### Criteria for discontinuing or modifying allocated interventions {11b}

The patient or treating clinician may withdraw from the trial at any time. The treating clinician may engage in Shared Decision-Making without accessing the decision aid (if in the usual care arm) or may not engage in Shared Decision-Making despite the use of the decision aid (if in the intervention arm). Subjects for whom an exclusion criteria becomes apparent after randomization (such as a new onset fever or newly discovered pregnancy) will be excluded from analysis and further study procedures and considered screening exclusions.

### Strategies to improve adherence to interventions {11c}

Fidelity to the intervention will be assessed via recording of conversations, if both participants and clinicians consent. Study staff will score in real time conversations that are not recorded using the OPTION-5 (*observing patient involvement*) scale [25].

### Relevant concomitant care permitted or prohibited during the trial {11d}

Clinical care will proceed as directed by treating clinicians. This will include various types of imaging, treatment, and follow-up plans. Department guidelines suggest the use of NSAIDS, anti-emetics, and tamsulosin upon discharge.

### Provisions for post-trial care {30}

No post-trial care is planned. Follow-up is via standard of care: primary care physicians and urology. Patients without primary care physicians will be given phone numbers for referral to primary care. The study site has 24-h urology on-call and available for all follow-up.

### Outcomes {12}

#### Outcome measures: feasibility and fidelity

As this protocol is for an adaptive design randomized trial, we intend to analyze outcomes at two points during the trial. The first interim analysis will examine only feasibility and fidelity to treatment arm (Fig. 3) and will occur after 50 participants are enrolled. Audio recordings of the conversation will be obtained to assess fidelity to the use of the decision aid (in the intervention group) and to monitor for contamination in the control group.

**Fig. 3 Fig3:**
[figure not shown]
Adaptive design: interim analyses

Recruitment will be considered feasible if > 3 participants are enrolled per month and the follow-up rate is at least 70%. Acceptability will be measured by a 7-point Likert scale, and the acceptability goal will be having > 50% of clinicians reporting the decision aid to be somewhat or extremely helpful. Regarding fidelity, a 3rd party will rate conversations on pre-defined criteria for SDM (OPTION-5 scale: *observing patient involvement*) [25]. If > 50% of intervention group conversations and < 30% of usual care conversations are rated as utilizing SDM, this condition will be considered satisfied. If two of three initial goals are not met (recruitment, acceptability, and fidelity), we will pause the trial and implement appropriate changes to the protocol.

#### Outcome measures: efficacy

We selected outcome measures via input from the Steering Committee, patients, and practicing clinicians as well as previous literature [26]. We also have included in the post-enrollment survey a measure assessing outcome priorities in the studied population. As stakeholders generally represent two different groups (patients and clinicians), we considered two outcomes as primary [27]. Clinicians endorsed radiation exposure as the most important primary outcome, measured as the proportion of patients receiving a CT scan during the ED visit and within 60 days and total radiation exposure in 60 days. Patients endorsed knowledge as a primary outcome, and the steering committee created and piloted a 10 question knowledge test.

We also selected a number of secondary outcomes based on stakeholder input. Secondary efficacy outcomes include 1 - clinician effort to engage patients in SDM (OPTION-5 scale), 2 - patient engagement as measured by CollaboRATE and SDM question(s), 3 - patient satisfaction (items from the Hospital Consumer Assessment of Healthcare Providers and Systems [HCAHPS]), 4 - trust in physician (trust in physician scale, 5 questions) and several implementation outcomes regarding the helpfulness of the intervention (see post-encounter patient and clinician data collection forms, Supplementary Materials 3 and 4) [25, 28, 29].

Safety outcomes include the primary outcome of radiation exposure (number of CT scans obtained on day 0 and within 60 days), total radiation in 30 days/60 days (milli-gray [mGy]) from diagnostic imaging, and the incidence of high-risk diagnoses with complications (HRDwC) that could be related to missed or delayed diagnoses. These HRDwC have been previously defined [10].

Operational outcomes will include (1) ED revisits (in 7/30/60 days) and hospital admissions on second visit, (2) ED length of stay (LOS) (minutes), (3) admission rate, (4) final diagnosis for initial visit, (5) 60-day alternative diagnoses, and (6) urologic procedures (in 30/60 days).

Implementation outcomes will include (1) clinicians’ ratings of conversation/decision aid (“would you recommend,” “would you use again,” and qualitative feedback), (2) acceptability (clinicians’ ratings, qualitative and quantitative), and (3) Fidelity (RA checkboxes) as well as adherence to protocol.

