## Statistical methods

### Statistical methods for primary and secondary outcomes {20a}

For the primary outcome, the univariable comparison of study groups on the proportion of CTs obtained will be conducted using Pearson’s chi-square. Univariable comparisons of study groups on questionnaire outcomes (e.g., patient knowledge, patients satisfaction) will be conducted with independent sample t-tests.

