### Interim analyses {21b}

The first interim analysis, which will occur after 50 patients are enrolled, will only consider feasibility and fidelity of the protocol (i.e., whether recruitment and retention goals are met, whether the protocol is acceptable to clinicians, and whether the protocol is being administered as planned). There will be no planned assessment of efficacy outcomes at this interim analysis. As such, there will be no adjustment to the *p* value for this interim analysis.

At the second interim analysis (approximately 100 patients evaluable for efficacy), we will evaluate the sample to determine whether further enrichment of the sample is required (e.g., further refinement of inclusion/exclusion criteria, such changing the maximum age or excluding patients with a history of ureterolithiasis). We will assess efficacy as this interim analysis, and therefore will adjust the critical test level accordingly. Using the O’Brien-Fleming approach to the alpha spending function, one evaluable interim look at approximately 50% of the sample, the critical test levels for early termination for efficacy will be *p* ≤ 0.003 and *p* ≤ 0.047, for a two-sided test [36, 37]. That is, if at the first evaluable interim analysis the difference between study groups in both primary outcomes achieves a significance level of *p* ≤ 0.003, the study will stop. The final significance test will be conducted at *p* ≤ 0.047, rather than *p* ≤ 0.05.

Initial data analysis will describe the distribution of all outcomes by treatment group. Continuous measures will be reported using means, standard deviations, medians, and percentiles. Categorical measures will be reported using frequencies and percentages. Rather than testing baseline covariate imbalance, stratified analyses will be conducted for baseline covariates that are known to be strongly associated with outcomes, as well as those that show imbalance on inspection [38].

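### Two primary outcomes meet one final level of 0.047 with no stated success rule, the radiation primary is not a single measure, and 0.047 is not the value the named boundary gives

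*Protocol article*

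**What the plan says.** Under *Outcome measures: efficacy* the protocol says "we considered two outcomes as primary". One is knowledge ("Patients endorsed knowledge as a primary outcome"). The other is radiation, worded as "proportion of patients receiving a CT scan during the ED visit and within 60 days and total radiation exposure in 60 days". Later in that section, in the paragraph on safety outcomes, the radiation primary is described as a number of CT scans on day 0 and within 60 days, and total radiation is listed as a separate item.

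Under *Interim analyses {21b}* the trial stops early "if at the first evaluable interim analysis the difference between study groups in both primary outcomes achieves a significance level of" 0.003. The final step reads "The final significance test will be conducted at *p* ≤ 0.047". The stated basis is an O'Brien-Fleming spending function with one efficacy look at about half the sample, two-sided.

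*Statistical methods for primary and secondary outcomes {20a}* uses the singular: "For the primary outcome, the univariable comparison of study groups on the proportion of CTs obtained" is made by chi-square, with no time point. Knowledge appears there as an example of a questionnaire outcome, tested by t-test.

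*Sample size {14}* powers CT use at 0.047 and powers knowledge separately, with neither a standard deviation nor a test level.

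**The concern.** The primary outcomes, the stopping rule and the final level are all fixed in this document, and they do not fit together. Three readings of the final analysis are open: one primary outcome (the statistical methods section), two that must both succeed (by extension of the interim rule), or two of which either is enough (the single level, with no rule attached). The radiation primary also leaves open the time point, whether it is a proportion or a count, and whether total dose belongs to it.

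At stake is whether a positive primary claim carries the 5% protection that the interim adjustment was meant to preserve. The second interim analysis looks at efficacy and may change eligibility. A rule or measure settled after that look could be chosen with knowledge of the results.

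**Working it through.** **1. The plan's own power figure.** Inputs from *Sample size {14}*: 80% against 60%, 100 per group, two-sided 0.047 (z = 1.9863).
- Standard error under the null (pooled proportion 0.70): √(2 × 0.70 × 0.30 / 100) = 0.0648.
- Standard error under the alternative: √((0.80 × 0.20 + 0.60 × 0.40) / 100) = 0.0632.
- (0.20 − 1.9863 × 0.0648) / 0.0632 = 1.127, so power is 87.0%. The stated 87% reproduces.
- With 90 per group it is 83.3%, against the stated figure of about 80%.

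This power uses the whole of 0.047 for CT alone.

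**2. Error at the end, by success rule.** Each outcome is tested at 0.047 and no true effect exists on either.
- Either suffices, independent outcomes: 1 − (1 − 0.047)² = 9.2%. By simulation, 8.9% at a correlation of 0.3 and 8.5% at 0.5. Adding the early-stopping rule leaves these unchanged at this precision.
- Both required: 0.047² = 0.2% if independent, rising to 0.9% at a correlation of 0.5. If one outcome truly responds, the chance of a false joint claim is bounded by the level of the other test, so it stays below 5%.
- Either suffices, and the three radiation measures count as separate claims beside knowledge: the documents give no correlations, so these are assumed, with knowledge uncorrelated.

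| Assumed correlation among radiation measures | Chance of at least one false claim |
|---|---|
| 0.5 | 16.0% |
| 0.7 | 14.6% |
| 0.8 | 13.6% |
| 0.9 | 12.2% |
| 0.95 | 11.3% |

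**3. The boundary.** Inputs from *Interim analyses {21b}*: O'Brien-Fleming spending, one look at information fraction 0.5, two-sided 0.05.
- One-sided amount spent at the look: 2 × [1 − Φ(2.2414 / √0.5)] = 0.001525. Two-sided this is 0.00305, which agrees with the stated 0.003.
- The final critical value c solves P(|Z₁| < 2.963 and |Z₂| < c) = 0.95 with correlation √0.5. This gives c = 1.9686, a nominal level of 0.0490.
- Classical O'Brien-Fleming gives 0.0052 and 0.0480. Applying the spending function to the two-sided 0.05 as a whole gives 0.0056 and 0.0478. Neither pairs 0.003 with 0.047.
- The stated pair, 0.003 and 0.047, uses 0.0480 in total for one endpoint that could cross at either look. With 0.049 the total is 0.0500.
- CT power at 0.049: (0.20 − 1.9686 × 0.0648) / 0.0632 = 1.145, or 87.4%, a gain of 0.4 points.

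**4. What a joint or ordered rule does to power.** The plan gives no standard deviation for knowledge. A 2-point difference, 35 per group and 80% power imply roughly 2.9 to 3.0. Taking 2.95, with 100 per group and level 0.049, the standard error is 2.95 × √(2/100) = 0.417. Joint power is the product with CT power of 87.4%, assuming independence.

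| True knowledge difference | Knowledge power | Joint power |
|---|---|---|
| 2 points | 99.8% | 87.2% |
| 1.25 points | 84.8% | 74.1% |
| 1 point | 66.6% | 58.2% |

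**The case against.** The strongest reply is that no sentence says either primary is enough. The only decision rule actually written, for early stopping, requires both, and the final level follows it directly. If that rule carries over to the end, error is well controlled. A reader might infer from the single 0.047 that the protocol runs a false-claim risk of 9% to 15% as written. The text does not support that inference: the figure belongs to one permitted reading. This part of the objection stands.

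A reader might also count four primary tests. The protocol counts two outcomes, powers radiation only on CT use, applies its primary test only to the proportion of CTs, and in one place lists total dose separately. The 11% to 16% range therefore needs separate claims that the document does not set up, plus correlations that it does not give. This stands too.

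The boundary discrepancy is conservative and small. It must not be read as part of the inflation, and how 0.047 was derived is not shown (it happens to equal 0.05 − 0.003).

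Finally, splitting error across co-primaries can be left to an analysis plan that is not shown. That excuses missing detail. It does not excuse sections that disagree on whether there are one or two primary outcomes, or a stated final level that does not follow from the stated method.

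**Conclusion.** The point holds as an unresolved decision rule. The number of primary outcomes, the content of the radiation primary and the condition for final success are not fixed consistently. Depending on the rule adopted, the chance of a false primary claim when nothing works runs from under 1% (both required) to about 9% (either suffices). The 9% figure assumes an either rule and a correlation between the two outcomes of 0 to 0.5. The higher range of 11% to 16% is an outer case resting on assumed correlations and on treating every radiation measure as its own claim.

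The final level of 0.047 is confirmed as inconsistent with the named O'Brien-Fleming spending function, which gives 0.049. The error is on the safe side and costs about 0.4 points of CT power.

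**What to change.** Make these changes by amendment before the second interim analysis:

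- Name one radiation measure with one time point as primary, use the same wording in the outcomes, sample size and statistical methods sections, and make the other radiation measures secondary.
- State the final success rule. Requiring both primaries matches the interim rule. A pre-set fixed order, each step at the full final level, is an equally valid choice, and knowledge first is only one possible order.
- State the final level as 0.049.

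None of this needs more patients under the planned assumptions, but it is not free of consequences. Under a both rule, or with knowledge tested first, a CT claim depends on knowledge succeeding. Joint power stays near 87% only if the 2-point knowledge effect holds at the back-solved standard deviation, and it falls as shown above if the effect is smaller. With CT first, the knowledge claim depends on CT instead.

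Splitting the level, at about 0.0245 each, avoids that dependence and gives 1 − (1 − 0.0245)² = 4.8% under independence. CT power then drops to 80.4% at 100 per group and 75.7% at 90, and about 118 per group (236 in total) would be needed to restore 87%.

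The choice of time point also has a price. A 60-day CT measure is exposed to loss to follow-up, for which the feasibility criterion accepts retention as low as 70%. CT at the visit is not exposed to it.

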#### Integrating patient recruitment, consent, and delivery of the intervention in the flow of patient care

Figure 2 shows how the process of patient recruitment, consent, randomization, and delivery of the intervention will integrate with the flow of patient care. We will assess patient eligibility and obtain consent shortly after the clinician has evaluated the patient, treated their pain, and begun diagnostic testing (but prior to ordering a CT scan). Patients will then be randomized and receive the intervention or usual care. Patients for whom an exclusion criterion becomes apparent post-randomization (ex. patient who develops a fever, has a positive pregnancy test, or is found to have a solitary kidney on ultrasound) will be classified as screen failures and not analyzed [24].

Patients who are randomized to the decision aid arm will then be given the decision aid, and the clinician will be prompted to discuss the diagnostic options. For the purposes of blinding, patients randomized to usual care will receive a paper informational sheet and the clinician will be prompted to proceed with usual care regarding diagnostic imaging.

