## Assignment of interventions: allocation

### Sequence generation {16a}

#### Randomization

Patients will then be randomized via permuted blocked randomization [31, 32]. Randomization will be stratified by “history of stones” with separate randomization for subjects with a history of kidney stones, as the decision aid for these patients is different, because guidelines suggest avoiding CT for young healthy patients with a history of kidney stones [33]. Allocation will be based on a 1:1 ratio between the intervention and usual care arms. Though we will not be able to blind clinicians to use of the decision aid, patients will not be aware of whether they are receiving usual care or the decision aid, as the consenting information will refer to paper-based information—which accurately describes both the decision aid and the usual care information packet. The research staff will maintain a database recording randomization, which will be separate from general subject-level data and will not be accessible to the PI or statisticians until planned interim analyses.

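### ED length of stay, in its ordinary arrival-to-departure sense, includes time before randomisation that the aid cannot change; adjusting for that time would cheaply sharpen the comparison

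*Protocol article*

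**What the plan says.** Under Outcomes {12}, Outcome measures: efficacy, the article names "2) ED length of stay (LOS) (minutes" as the second of six operational outcomes. It gives no clock start, clock stop, hypothesis, power statement or decision rule for it.

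The section on integrating recruitment and consent into the flow of care has staff check eligibility first, then "obtain consent shortly after the clinician has evaluated the patient, treated their pain, and begun diagnostic testing (but prior to ordering a CT scan"). Allocation comes next: "Patients will then be randomized and receive the intervention or usual care". In the intervention arm, after allocation, "the study coordinator will give the patient at least 15 min to read the decision aid prior to discussion with the clinician" (Intervention description {11a}).

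Under Multivariable analyses, regression adjusts for baseline characteristics that look imbalanced or show moderate to large standardised effect sizes. Covariates that barely move the treatment estimate and add nothing to clinical interpretation may be dropped. Under Interim analyses {21b}, stratified analyses are planned for baseline covariates known to be strongly related to outcomes and for those that look imbalanced. Time before randomisation is named in neither place.

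**The concern.** Length of stay in the usual sense is the sum of two parts: arrival to randomisation, and randomisation to departure. Waiting, evaluation, analgesia, the start of testing and consent fall in the first part. Anything the aid does to the stay falls in the second: reading time and discussion may lengthen it, and fewer CT scans may shorten it. Unless the two parts are sufficiently negatively correlated, the first part adds variance and no signal.

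The stake is precision on an outcome tied to the trial's rationale: the Background lists time in the ED among the trade-offs that make this decision suitable for shared decision-making. The adjustment rule is unlikely to help. A covariate chosen for precision is balanced by design in expectation and usually changes the estimate little, so a rule that looks for imbalance, or for movement in the estimate, tends to pass it over.

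**Working it through.** **The plan's own figure.** There is none for length of stay. The only stated power with 100 per group is for CT use (80% against 60%, two-sided 0.047). A pooled-variance normal approximation gives 87.0% against the stated 87%. This confirms the group size used below and has no other bearing on length of stay.

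**Inputs.**
- From the article: 100 per group (Sample size {14}); "Allocation will be based on a 1:1 ratio between the intervention and usual care arms"; randomisation after part of the stay.
- Assumed, because the documents give nothing: SD after randomisation 120 min; SD before randomisation 60 to 120 min; the two parts independent; two-sided alpha 0.05.

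**Expected difference.** The part before randomisation has the same distribution in both arms, so the expected arm difference is the same with or without it.

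**Precision.** Total SD = √(SD_post² + SD_pre²); SE = SD × √(2/100); difference detectable with 80% power = 2.802 × SE; 95% half-width = 1.96 × SE.

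| Quantity | Total stay, SD_pre 60 | Total stay, SD_pre 120 | Adjusted for time before randomisation |
|---|---|---|---|
| SD (min) | √(60² + 120²) = 134.2 | √(120² + 120²) = 169.7 | 120 |
| SE (min) | 19.0 | 24.0 | 17.0 |
| 95% half-width (min) | 37 | 47 | 33 |
| Detectable difference (min) | 53.2 | 67.2 | 47.5 |

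SE ratios: 120/134.2 = 0.894 and 120/169.7 = 0.707, a fall of about 11% to 29%. These ratios do not depend on the group size.

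**Sensitivity.** With SD_post from 90 to 180 min and SD_pre from 30 to 120 min, including the earlier part raises the detectable difference by between 1% and 67%. In unit-free terms, take a difference that has 80% power on time after randomisation. Its power on total stay is 76% if the earlier part makes up 10% of total variance, 65% at 30% and 51% at 50%.

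**A 15-minute effect.** 15/17.0 = 0.88 standard errors, which gives power of about 14% after adjustment. On unadjusted total stay it is about 12% (SD 134) or 10% (SD 170).

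**Subtracting or adjusting.** Var(total) = SD_post² + SD_pre² + 2ρ·SD_pre·SD_post. This falls below SD_post² when ρ < −SD_pre/(2·SD_post), that is, −60/240 = −0.25 or −120/240 = −0.50. Below those correlations, unadjusted time from randomisation is noisier than total stay. Regression avoids this. Total stay minus earlier time is later time, so regressing either one on arm and earlier time gives the same arm coefficient; only the coefficient of earlier time shifts, by one. The residual SD is SD_post·√(1 − ρ²), which in large samples is never larger than the SD of total stay or of time from randomisation.

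**The case against.** The strongest reply is that the article never says length of stay is counted from arrival and names no test for it. An article may leave both to the full protocol or analysis plan. This stands. A reader might infer that the plan fixes an unadjusted arrival-to-departure comparison; the document does not state that, and the point rests on the ordinary meaning of the term.

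A reader might also infer that late randomisation biases the comparison. It does not: time before allocation is balanced in expectation. Total ED stay is a legitimate operational measure in a pragmatic trial, and using it is no error.

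It is tempting, too, to say that the reading time of "at least 15 min to read the decision aid prior to discussion with the clinician" would be rescued by removing the earlier noise. The working shows otherwise. Nor is 15 minutes the expected arm difference, since usual-care patients also receive a pamphlet and fewer CT scans could shorten the stay in the intervention arm.

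It can further be said that existing text leaves room for the adjustment, through regression on baseline characteristics and stratified analyses of strong predictors. It does leave room. But the regression rule selects on imbalance, the stratified analyses do not name this variable, and neither provision secures the time stamp.

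**Conclusion.** The point holds as a minor improvement in precision. Under the ordinary reading of length of stay, time that allocation cannot affect enters the outcome, and the stated adjustment rule would usually not bring in the covariate that removes it. There is no bias, and no sample size, significance level, stopping rule or primary conclusion changes.

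The size cannot be computed from the documents. The 11% to 29% fall in standard error rests on the assumed SDs and on independence of the two parts, and the wider grid shows that the gain could be negligible or substantial. The claim that adjustment is no less precise is a large-sample one. Adjustment leaves the expected difference unchanged, but the estimate in a given sample will move.

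**What to change.** State the start and stop of the length-of-stay clock and keep total stay in minutes as the reported metric. Record the time at which each envelope is opened. Estimate the arm difference in length of stay by linear regression on arm and arrival-to-randomisation minutes, specified in advance and kept whatever the observed imbalance. Do not rely on unadjusted time from randomisation alone, which can lose precision if early and late time are negatively correlated.

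The cost is one time stamp and one covariate. Research staff already assign patients from the envelopes and enter data directly where possible. The stamp should be taken at randomisation, since it may be hard to recover accurately later.
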